# Structured Scientific Abstract

Depression is more common in MS than in many other chronic illnesses with 50-60% of MS patients affected by depression. Supplementation with omega-3 fatty acids has been reported to significantly reduced depression and to have low side effects in subjects with unipolar depression that were on stable doses of anti-depressant medication. Omega-3 fatty acid supplementation, in the form of fish oil, may offer a safe adjunctive therapy to improve the therapeutic benefits of antidepressants in MS. The primary aim of this pilot study is to determine if fish oil supplementation is an effective and safe adjunctive treatment for mild to moderate depression in people with MS. This will be a 3-month randomized, double blind, placebo controlled pilot trial of fish oil supplementation for the treatment of mild-moderately depression people with MS. Subjects in both the placebo and fish oil group that have responded to treatment (> 50% improvement on either the Montgomery-Asberg Depression Rating Scale (MADRS) or Beck Depression Inventory (BDI)) will have the option to continue on treatment for an additional 3 months to evaluate longer-term effects. Treatment during this continuation phase will remain blinded. Sixty subjects age 18-65 years old with a definite diagnosis of MS that have been diagnosed with major depressive disorder (MDD), based on the Structured Clinical Interview for DSM-IV (SCID), will be randomized to one of two groups: placebo or 6.0 g/day fish oil supplementation (2.1 g/day EPA, 1.5 g/day DHA). All subjects will maintain stable doses of their pre-study antidepressant and MS disease modifying medications while participating in the study.

Our primary objective, Aim 1, is to determine the treatment effect on depression by using the MADRS and BDI. We will also monitor adverse events by subjects self-report of general health and laboratory tests (metabolic panel, including liver function tests and prothrombin time). We will monitor worsening of depression and suicidal ideation using both depression inventories, BDI and MADRS. Our secondary objective, Aim 2, is to determine the treatment effect on inflammatory cytokine levels, as fish oils may exert its clinical effect by decreasing peripheral levels of proinflammatory cytokines. We will measure cytokines released from mitogen stimulated peripheral blood mononuclear cells (PBMCs) by immuno-assay. Compliance will be monitored by pill count and red blood cell fatty acid analysis. Data collected from this pilot study will be used to aid us in the design of a larger, multi-center clinical trial that could more fully evaluate the effectiveness of this therapy.

**A. SPECIFIC AIMS**

Aim 1) To determine if fish oil supplementation is an effective and safe adjunctive treatment for mild to moderate depression in people with MS

A. We hypothesize that 3 months of fish oil supplementation will improve depression scores on the Montgomery-Asberg depression rating scale (MADRS) or Beck Depression Inventory (BDI) more than the placebo treated group. Subjects in both the placebo and fish oil group that have responded to treatment (> 50% improvement on MADRS or BDI) will have the option to continue on treatment for an additional 3 months to evaluate longer-term effects.

B. We hypothesize that fish oil at the doses given is safe in MS subjects with mild to moderate depression taking MS disease-modifying drugs and anti-depressants. We will monitor the following: effects on blood clotting by prothrombin time (PT/INR); metabolic function including liver function by comprehensive metabolic panel; adverse events reporting (includes subject’s report of general health and screening for worsening of depression by BDI and MADRS).

Aim 2) To determine the effects of fish oil supplementation on pro-inflammatory agents related to depression and MS.

We hypothesize that one mechanism by which fish oil may exert its clinical effect is by decreasing peripheral levels of proinflammatory agents (cytokines). We expect to see a decrease in peripheral levels of inflammatory cytokines in subjects treated with fish oil.

We will measure the following cytokines release from mitogen stimulated peripheral blood mononuclear cells (PBMC) at 2 baseline time points and then at 1, 3, & 6 months of supplementation: tumor necrosis factor alpha (TNF-α), interferon gamma (IFN-γ), interleukin 2 (IL-2), interleukin-6 (IL-6), interleukin-4 (IL-4), and interleukin-10 (IL-10).

**B. BACKGROUND and SIGNIFICANCE**

It is estimated that 50-60% of patients with MS are affected with depression [1]. Although antidepressants show great benefit in alleviating depression, 29%-46% of depressed patients show a partial to no response to antidepressant therapy [2]. The treatment strategy for these patients includes increasing medication dose, switching to a different type of antidepressant medication, or augmenting current medication with an additional antidepressant [3]. All of these strategies pose safety concerns which include: lack of safety evidence for these strategies, severe side effects while switching therapies, potential for “serotonin syndrome” when combining two antidepressant agents [3]. Identifying safe and effective adjunctive therapies for depression in MS is warranted given the high prevalence of depression and the high use of anti-depressant medication in this population. The omega-3 fatty acids have been reported to improve depression when used as an adjunctive therapy in unipolar depression [4-6]. Because an increase in inflammatory mediators have now been associated with depression in MS [7, 8], omega-3 fatty acid supplementation may offer clinical benefit by decreasing peripheral levels of pro-inflammatory mediators. As fish oils possess strong anti-inflammatory properties, its adjunctive value for depression may be of special importance in inflammatory diseases in general.

#### Inflammatory cytokines may contribute to depression in MS

Major depression is associated with activation of the inflammatory response system (IRS) that includes increased numbers of leukocytes, activated T-cells and neurophils resulting in an increase in the production PGE2, TNF-, IFN-, interleukin-1 beta (IL-1), interleukin-6 (IL-6), and cytokine receptors for IL-1 (IL-1R) and interleukin-2 (IL-2) [9-18]. Although the mechanisms by which inflammatory mediators induce depression have not been elucidated, it is suggested that they may act by disrupting the hypothalamo-pituitary-adrenocortical (HPA) axis [19] or by indirectly decreasing CNS serotonin levels by catabolizing tryptophan in the periphery [20, 21]. This body of evidence linking major depression to activation of inflammatory response is of particular interest in MS as some of the same pro-inflammatory mediators implicated in major depression are implicated in MS immunopathogenesis.

There are two reports examining the association between depression, inflammatory cytokines, and MS [7, 8]. The first reported a significant positive correlation between TNF-α (r =.55) and IFN-γ (r =.54) mRNA expression levels and the BDI sum scores in MS patients. The second reported a significant positive correlation between baseline BDI score and IFN-γ production (r =.64) in 14 subjects with relapsing-remitting MS diagnosed with MDD [8].

Conventional treatments for depression in MS

Conventional treatment for depression in MS includes antidepressant medication, individual psychotherapy, and group psychotherapy. Antidepressant medication is probably the most widely used therapy for depression in MS. Very few studies evaluating the efficacy of antidepressants in MS have screened patients for major depressive disorder using DSM-IV criteria for depression [22]. One comparative study evaluating the effect of antidepressant therapy for MDD in MS reports that treatment significantly reduced depression as measured by the BDI. The study randomized 63 subjects that met criteria for both MS and major depressive disorder to one of three treatment groups: individual cognitive-behavioral therapy, supportive-expressive group therapy, or treatment with sertraline. Clinical outcomes using a 50% reduction from the baseline score of the BDI as a response criterion found that only 24% (n=5) of the sertraline group achieved significant improvements. The authors suggest that although depression in MS is responsive to treatment, it is more difficult to treat than suggested in previous studies (76% of the sertraline group did not achieve significant improvements in depression scores).

#### Omega-3 fatty acids a safe adjunctive treatment for depression

- There are three reported double-blind placebo controlled pilot studies evaluating the effects of omega-3 fatty acids in depression. All three studies report a significant improvement depression in subjects treated with omega-3 fatty acids. The first was a study of 20 patients diagnosed with MDD using DSM-IV criteria. Subjects were enrolled if they met criteria for MDD, had a baseline score on the HDRS (17 item) of > 18, were 18-75 years old, had no alcohol and drug abuse, no psychotic features, and had no comorbid psychiatric diagnosis other than obsessive-compulsive disorder, panic disorder, or dysthymic disorder [5]. Subjects maintained their pre-study doses of antidepressant medication and were randomized to one of two groups: placebo or 2g/day ethyl-eicosapentaenoic acid (E-EPA), a type of omega-3 fatty acid. After 4 weeks there was a significant improvement in mean HDRS scores for the fish oil group compared to the placebo group, E-EPA 11.6 + 6.2, placebo 20.0 + 8.8; (p<0.001). The second study was a dose-ranging pilot study on the effects of E-EPA for depression [4]. In this study 70 patients were randomized to 1 of 4 treatment groups: placebo, 1g/day E-EPA, 2 g/day E-EPA, 4 g/day E-EPA. Treatment efficacy was assessed by the HDRS (17 item), the Montgomery-Asberg Depression Rating Scale (MADRS), and the BDI at 4, 8, and 12 weeks. All subjects maintained their pre-trial doses of antidepressant medication throughout the trial. By week 12, a significant improvement in depression by all three measures was achieved in the 1g/day group compared to controls and the other two doses. The authors noted that all doses of E-EPA were well tolerated, there were no dropouts in this study, and the most common side effect in the treatment group was mild and transient gastrointestinal upset. The authors conclude that E-EPA at 1 g/day significantly improves depression in people that are currently taking antidepressants. The investigators note that although their study found efficacy at the 1-g/day dose, other patients may require higher doses of E-EPA.

The third study used methodology similar to the first study except that subject’s received either placebo oil or fish oil (five 1-gram capsules per day containing 2.20 g EPA and 1.10 g docosahexanoic acid (DHA)). The HDRS was used to assess depression. After 8 weeks of treatment there was a significant difference in mean HDRS, placebo 15.7 + 3.7 and fish oil 8.9 + 3.2 (p<0.001) [6].

#### Omega-3 fatty acids possess anti-inflammatory actions

The immunomodulatory effects of omega-3 fatty acids have been well documented in scientific studies*. In vitro*, animal, and, *ex vivo* human studies have reported a decrease in mRNA and protein levels of a number of cytokines including TNF-α, IFN-γ, IL-1, IL-2, VCAM-1 [23]. A single published study reported a significant decrease, from baseline, in the levels of IL-1β (p<0.03), TNF-α (p<0.02), IL-2 (p<0.002), and IFN-γ (p<0.01) produced from unstimulated and stimulated PBMC of twenty MS subjects and fifteen healthy controls after three months supplementation with fish oil [24].

Conclusions

Antidepressant medication is a widely used and effective treatment for depression in MS; however, even with treatment many MS patients still experience mild to moderate depression. The same pro-inflammatory cytokines involved in MS disease pathogenesis are now implicated in the pathogenesis of major depressive disorder. Fish oil supplementation is reported in a number of studies, including one MS study, to decrease levels of peripheral pro-inflammatory cytokines and may exert its clinical effect by this mechanism. Fish oil may offer a safe and effective adjunctive therapy for depression in MS patients.

# C. PRELIMINARY STUDIES/PROGRESS REPORT

We have baseline data on depression scores from the BDI from 37 subjects that had participated in a naturopathic treatment pilot study in MS. Of the 37 subjects, 44% (16/37) were on antidepressants and 84% (29/37) were on one of the MS disease modifying medications. Of the 16 subjects taking antidepressants 7 subjects scored > 17 on the BDI. We compared this group with a group of 9 subjects taking anti-depressants that scored <17 on the BDI-21, mean = 6.4, s.d. + 4.2 and found that the group mean scores were significantly different, p=0.002. These results indicate that 44% (7/16) of study subjects on antidepressant therapy are still scoring significantly high on the BDI.

# D. RESEARCH DESIGN and METHODS

#### *Overall study design*

Phase I of this study will be a 3-month randomized, double blind, placebo controlled pilot trial. There will be 7 visits over the course of 3-months. Sixty subjects age 18-65 years old with a definite diagnosis of MS [25] that have been diagnosed with MDD, based on the Structured Clinical Interview for DSM-IV (SCID), will be randomized to one of two groups: placebo or 6.0 g/day fish oil supplementation (2.1 g/day EPA, 1.5 g/day DHA). All subjects will maintain stable doses of their pre-study antidepressant and MS disease modifying medications while participating in the study. Subjects in both the placebo and fish oil group that have responded to treatment (> 50% improvement on MADRS or BDI) will have the option to continue on treatment for an additional 3 months to evaluate longer-term effects, Phase II of this study. There will be 3 visits during Phase II and treatment during this phase will remain blinded. Clinical and biological measures will occur at baseline and 1, 3 & 6 months of supplementation.

#### **Study visits**

#### Prescreening (phone contact)

All potential subjects will be prescreened by a telephone interview. The potential subject will be asked about whether or not they meet the study inclusion and exclusion criteria. Those who meet preliminary inclusion by the phone screen will be scheduled for an in-clinic screening visit at OHSU.

#### Visit 1 (Screen)

The screening visit is to establish eligibility for study participation. This visit and all subsequent visits will take place at the MS Center of Oregon at OHSU or at the General Clinical Research Center (GCRC) at OHSU. Each potential study subject will be consented at this visit after which a family and medical history will be taken. The subject will be screened for major depressive disorder using the SCID, dementia by the MMSE, and for mild to moderate depression using the MADRS. They will then be asked to fill out the BDI. Concomitant medications will also be recorded at the screening visit (*See Table 1: Study Schedule: Phase I*).

Visit 2 (Baseline)

Subjects that meet study inclusion after the screening visit will be scheduled for follow up within 2 weeks. At this visit subjects will receive a brief physical exam and a neurological exam (EDSS) from [name]. The subject will be given a MADRS score. A research assistant will administer the MS Functional Composite (MSFC) and record concomitant medications. The subject will fill out study questionnaires which include: BDI, Multiple Sclerosis Quality of Life Inventory (MSQLI), and Food Frequency. A research assistant will draw blood for cytokine levels, prothrombin time (PT/INR), comprehensive metabolic panel, and RBC fatty acid analysis.

#### Visit 3 (day 0)

#### This visit will occur one week after baseline. At this visit, subjects will receive study medication for 1 month and be instructed on the dose.

#### Visit 4 (week 2)

At this visit subjects will be screened for worsening of depression (>30 on the BDI) and suicidal ideation using question #9 from the BDI. If either of these occurs the subject will be immediately referred for standard care and will be exited from the study. General health adverse events will also be recorded at this visit. [name] will be available by pager 24 hours a day to address patient safety issues. [name] will be available to discuss these cases with [name]. The subject will be instructed to bring their medication bottle to their next scheduled visit.

Visit 5 (week 4)

All measures except PE/neurological exam/EDSS, the Food Frequency questionnaire, and the MSFC will be assessed at this visit. A research assistant will draw blood for prothrombin time (PT/INR), comprehensive metabolic panel, cytokine levels, and RBC fatty acid analysis. A research assistant will assess the subject for adverse events and perform a pill count. The subject will also be asked about any changes in medication or doses of medications (prescribed and over the counter). The subject will be instructed to bring their medication bottle to their next scheduled visit.

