#### Visit 6 (week 8)

MADRS and BDI will be administered. A research assistant will assess the subject for adverse events and perform a pill count. The subject will also be asked about any changes in medication

or doses of medications (prescribed and over the counter). The subject will be instructed to bring their medication bottle to their next scheduled visit.

Visit 7 (week 12)

This visit will assess all of the same measures as Visit 2. In addition, the subject will return all remaining study drug and a pill count will be performed. If the subject has achieved a 50% improvement on their BDI or MADRS score they may choose to continue on in the study for another 3 months or to exit the study. If the subject chooses to remain in the study, we will review the consent form for Phase II of the study and attain consent before proceeding with Phase II. After being consented the subject for the subject will receive another month’s supply of study medication and will be instructed to bring this bottle to their next scheduled visit.

Table 1. Study Schedule: Phase I

| **Assessments** | **Visit 1**  Screen | **Visit 2**  Baseline | **Visit 3**  Wk 0 | Phone  Wk 1 | **Visit 4**  Wk 2 | Phone  Wk 3 | **Visit 5**  Wk 4 | **Visit 6**  Wk 8 | Phone  Wk 10 | **Visit 7**  Wk 12 |
| --- | --- | --- | --- | --- | --- | --- | --- | --- | --- | --- |
| Family and Medical Hx | X |  |  |  |  |  |  |  |  |  |
| PE/Neurological exam/EDSS |  | X |  |  |  |  |  |  |  | X |
| SCID | X |  |  |  |  |  |  |  |  |  |
| BDI | X | X |  | X | X | X | X | X | X | X |
| MADRS | X | X |  |  |  |  | X | X |  | X |
| MMSE | X |  |  |  |  |  |  |  |  |  |
| MSQLI |  | X |  |  |  |  | X |  |  | X |
| MSFC |  | X |  |  |  |  |  |  |  | X |
| Cytokine measurement |  | X |  |  |  |  | X |  |  | X |
| Metabolic panel, PT time |  | X |  |  |  |  | X |  |  | X |
| RBC fatty acid |  | X |  |  |  |  | X |  |  | X |
| Food freq. survey |  | X |  |  |  |  |  |  |  | X |
| Concomitant medications | X | X |  |  |  |  | X | X |  | X |
| Adverse Events |  |  | X | X | X | X | X | X | X | X |
| Pill Count |  |  |  |  |  |  | X | X |  | X |
| Blinding evaluation |  |  |  |  |  |  |  |  |  | X |

Table 2. Study Schedule: Phase II

| **Assessments** | Month 4 | | Month 5 | | Month 6 | |
| --- | --- | --- | --- | --- | --- | --- |
| Phone  wk  14 | Visit 8 wk  16 | phone  wk  18 | Visit 9 wk  20 | phone  wk  22 | Visit 10 wk  24 |
| Family and Medical History |  |  |  |  |  |  |

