#### **Inclusion Criteria**

-Definite MS by McDonald criteria [25]

-Relapsing remitting course of MS

-Meets DSM-IV criteria based on SCID for Axis I disorders [31]

-Age 18 or older

- Scores between 11-30 on the MADRS (indicating mild to moderate depression) [26]

-Scores 25 or greater on the MMSE

-no essential fatty acid supplementation and < 6 oz per week of fish in diet at least 1 month prior to enrollment

-on stable dose of anti-depressant medication (no change in medication or dose at least 3 months prior to enrollment)

-on stable dose of interferon beta or glatiramer acetate (no change in MS disease modifying medication at least 6 months prior to enrollment)

-Able to understand and sign consent

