#### **Exclusion Criteria**

-Severe depression with suicidal ideation and plan as determined by SCID >20 and MADRS > 30

-Serious psychological disorders (e.g. psychotic disorders, bipolar disorder)

-Taking 2 or more antidepressants

-Plans to change antidepressant therapy within 3 months of enrollment

-Serious medical conditions such as congestive heart failure, cancer, liver disease, kidney failure.

-Current or past history of clinically significant ventricular arrythmias: includes patients that are receiving implantable cardioverter defibrillator (ICD) for sustained ventricular tachycardia (VT) or ventricular fibrillation (VF), or patients that had received an ICD or ICD therapy for an episode of VT/VF within the past 6 months, or subjects currently taking anti-arrythmia medications for VT/VF (e.g. Quinidine, Amiodarone).

-MS exacerbation or corticosteroid treatment 1 month prior to enrollment

-Pregnancy (pregnancy might alter results on outcome measures)

-Enrolled in another study

Because of the short duration of this study, subject participation will be stopped for the following reasons: MS exacerbation, change in MS disease modifying medication, and change or increase in antidepressant medication.

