The Data Safety and Monitoring Board of ORCCAMIND will monitor this study to ensure the safety of subjects. We will monitor adverse events by laboratory tests, which include prothrombin time (PT/INR) and comprehensive metabolic panel. For the first month of the study general health events, worsening of depression (>30 on BDI), and suicidal ideation (question # 9 on BDI) will be monitored weekly (2 x by phone and 1x in-clinic) for all subjects. If either of these occurs the subject will be immediately referred for standard care and will be exited from the study. [name] will be available by pager 24 hours a day to address patient safety issues. [name] will be available to discuss these cases with [name]. After the first month, subjects will be monitored every other week for general health events, worsening of depression (>30 on BDI), and suicidal ideation (question # 9 on BDI) (1 x by phone and 1x in-clinic). The same procedures described for month-1 will apply for all subjects throughout the study period. Subjects that have an acute MS exacerbation during the study will be referred to their neurologist for care.

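### The entry and on-study rules for suicidality do not match, so a subject with ideation but no plan can be enrolled and then meet the exit rule at the first check

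*Protocol*

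**What the plan says.** **Entry.** The protocol's Inclusion Criteria require "Scores between 11-30 on the MADRS (indicating mild to moderate depression") and set no condition on any single item. The only criterion that mentions suicidality is in the Exclusion Criteria: "Severe depression with suicidal ideation and plan as determined by SCID >20 and MADRS > 30". The Assessments section describes the SCID as a semi-structured diagnostic interview and defines no numerical score for it.

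**Before treatment.** At Visit 1, after the MADRS, subjects complete the BDI ("They will then be asked to fill out the BDI"). Table 1 schedules it again at Visit 2. Study capsules are first handed out at Visit 3, one week after Visit 2. The Randomization section uses the screening BDI score only to stratify. No rule refers to item 9 at either visit.

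**On study.** At Visit 4 subjects are "screened for worsening of depression (>30 on the BDI) and suicidal ideation using question #9 from the BDI". Section E.f (Protection against risk) repeats the rule for the first month: "suicidal ideation (question # 9 on BDI) will be monitored weekly (2 x by phone and 1x in-clinic"). The consequence in both places is: "If either of these occurs the subject will be immediately referred for standard care and will be exited from the study". Section E.f then extends it: "The same procedures described for month-1 will apply for all subjects throughout the study period".

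**Status of the check.** The abstract lists suicidal ideation among the things monitored with the BDI and MADRS, and section D sends the reader to section E.f for adverse event monitoring.

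**The concern.** The two rules use different definitions of the same concept. Exclusion at entry needs ideation, a plan and severe depression together. Exit on study needs only ideation on one BDI item, with no reference to a plan, no cut-off and no comparison with what the subject reported before treatment.

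The trial recruits people with a SCID diagnosis of major depression, so some may report ideation at baseline. Such a subject can be randomised, take capsules for a week or two and then have to leave for an answer that has not changed. Three things are at stake:

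- randomising people who already meet the exit rule;
- losing them before they provide any follow-up on either major outcome (the 3-month changes in MADRS and IFN-gamma);
- handling the same answer in two ways, with mandatory referral and exit after day 0 but no stated consequence at Visits 1 and 2.

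**Working it through.** The point rests on comparing the texts. The arithmetic only bounds its size.

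**Step 1: follow one subject through the rules.** Take MADRS 22, suicidal ideation on BDI item 9, no plan, BDI total 30 or below.

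| Stage | Rule that applies | Result |
|---|---|---|
| Inclusion, MADRS 11-30 | total score only | passes |
| Exclusion on suicidality | needs severe depression, ideation and a plan, MADRS above 30 | not excluded |
| Visits 1 and 2, BDI completed | no rule on item 9 | no stated consequence |
| Visit 3, day 0 | capsules dispensed | starts treatment |
| Week 1 call, or Visit 4 (week 2) | ideation on item 9 | referral and exit if the answer is unchanged |
| Visit 5 (week 4) | first post-baseline MADRS and cytokines | not reached |

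A limit on the MADRS or BDI total would not close the gap, because a total does not restrict a single item.

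**Step 2: check the exclusion itself.** A MADRS above 30 is already barred by the 11-30 inclusion range, so the exclusion removes nobody whom that range admits. Read literally, even ideation with a plan at MADRS 30 or below is not excluded. The SCID value above 20 has no meaning stated in the protocol.

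**Step 3: number affected.** The documents give no rate of baseline ideation. I assume a proportion p and full persistence to the first check.

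- Expected number: 60 × p.
- Chance of at least one: 1 − (1 − p)^60. At p = 0.05 this is 1 − 0.95^60 = 0.954.
- Chance that the arms differ by 3 or more such exits: from two independent binomials with n = 30.

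| p | Expected of 60 | At least one | Arms differ by 3 or more |
|---|---|---|---|
| 5% | 3 | 95% | 13% |
| 10% | 6 | >99% | 27% |
| 20% | 12 | >99% | 42% |
| 30% | 18 | >99% | 48% |

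**Step 4: effect on power.** Inputs from the sample size section are a difference of 9.3 HDRS units, SD 7.4 and alpha 0.05 (taken as two-sided). The standardised difference is 9.3/7.4 = 1.257. For a two-sample t-test the noncentrality is 1.257 × √(n/2) with 2n − 2 degrees of freedom.

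The plan's own figure first: 11 per group gives noncentrality 2.95 and power 80.1% (the exact solution is n = 10.99), so the stated 11 reproduces.

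As a pessimistic case, put these exits on top of the protocol's 20% dropout, so that n per arm = 30 × (1 − p) × 0.8:

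| p | n per arm | Noncentrality | Power |
|---|---|---|---|
| 5% | 22.8 | 4.24 | 98.6% |
| 10% | 21.6 | 4.13 | 98.1% |
| 20% | 19.2 | 3.89 | 96.6% |
| 30% | 16.8 | 3.64 | 94.2% |

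If the exits are instead counted inside the 20% allowance, the loss is smaller. At p = 20% they alone would use all of it (12 of 60).

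**The case against.** **Different thresholds can be deliberate.** Entry and exit rules need not be identical, and a stricter rule on study is not in itself a contradiction. That is fair. But the protocol gives no rationale, and it does not say what happens to a subject who meets the exit rule before the first capsule.

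**The exit rule may mean new onset.** It applies if worsening or ideation occurs, which could mean emergence on study. This reading is possible, so exit at the first check is not certain. But no comparison with baseline is stated, and the companion trigger, BDI above 30, is an absolute value. The two readings treat a subject with baseline ideation differently, so the text has to say which applies.

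**Stronger readings that the documents do not support.**

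- A reader might infer that these exits are recorded as on-treatment adverse events and inflate the safety counts. No sentence says so. Aim 1B names general health and worsening of depression under adverse event reporting, and Visit 4 mentions recording of general health events separately. Suicidal ideation is part of safety monitoring, but how it is tabulated may be settled in an analysis plan that is not at hand.
- A reader might infer a material loss of power. That requires a smaller effect than the protocol assumes, and the protocol states none.
- A reader might infer that staff do nothing about ideation at Visits 1 and 2. The protocol is silent, which is not the same thing.

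**Conclusion.** The mismatch stands, and nothing else in the protocol resolves it. As written, ideation without a plan at MADRS 11-30 does not prevent entry but is sufficient for exit, and the item 9 answers that would reveal the conflict are collected twice before treatment without any stated use. The exclusion is weakened further by its link to a MADRS range that is already barred and to an undefined SCID score.

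The size is unknown. The range of 3-18 subjects rests on an assumed 5-30% prevalence and full persistence, neither of which comes from the documents. Even at 5%, at least one such subject among 60 is very likely. The 94-99% power holds only if the protocol's HDRS effect and SD carry over to the MADRS.

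This should be corrected because it bears on subject safety and avoidable early attrition and is easy to repair. It does not undermine the nominal power of the trial.

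**What to change.** 1. Reconcile the Inclusion Criteria, the Exclusion Criteria, the Visit 4 text and section E.f so that the entry and exit rules on suicidality are consistent. Either side, or both, may change; that clinical choice belongs to the investigators.
2. State how the Visit 1 and Visit 2 item 9 answers are used, what response on item 9 triggers the on-study rule, and whether that trigger is absolute or relative to the pre-treatment answer.
3. Define the SCID value in the exclusion or remove it, and resolve the overlap between the MADRS limit in that criterion and the inclusion range. Bring the list of reasons for stopping participation, at the end of the Exclusion Criteria, into line, since it omits the item 9 exit.
4. Summarise on-study item 9 responses by arm against the Visit 2 response, so that ideation already present is distinguished from new or increased ideation.

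The cost is a short amendment and a line in the eligibility checklist or visit procedures. No new assessment is needed, and the summary in item 4 uses data already scheduled. Depending on the rule chosen, there may be a few more screen failures.
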